### Design Issues for analysis and sample size calculations

There are several important decisions we had to make in the design of the study that affect the analysis and sample size calculations for this study. The most important was whether our primary analysis was focused on the effectiveness or efficacy of the intervention. As noted above, pharmacist interventions have been shown to improve blood pressure in a variety of experiments that focused on randomly sampled individuals treated by research staff and who gave informed consent for the intervention prior to inclusion in the study. These are best characterized as trials of efficacy of the intervention.

Our study is intended to measure the ability to translate these findings into practice by deploying the intervention to clinic sites using staff and training that already exist or could easily be integrated into those settings and evaluating the impact on the entire population including those who ultimately decide not to accept the intervention. Thus, corresponding to an intention to treat analysis, all contacted patients, regardless of whether they were successfully contacted and enrolled in the intervention, will be included in the primary analyses. Patients will be analyzed within the group (intervention or control) they were assigned to at the time they first became eligible for the intervention. In this way the comparability of the patients in the intervention and control groups is maintained.

Another impact of this orientation on our design was that the perspective we took in our principal evaluation was that of the health center director, trying to decide whether to invest the resources to implement this intervention. In terms of the analysis plan, this meant that our principal analysis was whether teams that were randomized to the AIM intervention had a larger sustained decline in blood pressure among patients eligible for the intervention than teams that were randomized to the control intervention. We felt the most compelling argument could be made if the intervention group had a larger decline in the average blood pressure as measured by comparing the 6 months after the intervention year to the 6 months prior to the start of the intervention.

It was felt to be important to use blood pressures obtained through routine care to assess the impact of the intervention, again to maintain comparability to the control group who would otherwise have to be invited for special visits to measure their baseline and post-intervention blood pressures. As the number of measurements may vary and thus provide more or less precise estimates of the two endpoints, it is not possible to simply construct a difference between the average pre- and post BPs. We will use all data when multiple measurements allow us to estimate a change in BP more precisely as well as those observations in which only 1 measurement occurs in each period with weighting to reflect the varying precision of the estimates.

A three-level multilevel model will allow us to do this with the multiple individual BP measurements (both pre and post intervention) at level 1 nested within patient identifier at level 2 and team at level 3. An indicator variable will represent whether the BP is from the pre or post period coded so that the coefficient estimates the change in mean BP for the control group. The coefficient of an indicator variable representing treatment teams will estimate the mean BP difference between treatment and controls in the baseline period. The primary hypothesis will be tested by an interaction term between the treatment group indicator and the time period indicator variables. The multilevel structure of the model will account for the varying precision with which the BP endpoints are estimated and the clustering of patients within teams. Site will be included as a fixed variable.

We want to be able to describe reasons for the diminution or failure of the intervention to reduce blood pressure relative to effect sizes seen in the prior efficacy studies, particularly if those factors are amenable to changes in protocol that could ameliorate their impact. While it is possible that a successful intervention will show persistence of effect into the 6 month post-intervention window, it is possible that we will lose some power to detect an effect by sample loss if patients do not have recorded blood pressures during that period. Furthermore, some patients will have received the intervention early in the course of the intervention period and thus may be as much as 1 year out from the intervention when the 6 month post-intervention period ends and would have become eligible for repeat enrollment and improvement in the blood pressure if the intervention were an ongoing program at the site.

Therefore, a secondary analysis will examine the blood pressure slope starting at the point where patients are activated (initiation of contact for the intervention). Blood pressure changes will be looked at as a function of time after activation. As the activation is determined by random sampling from the list of eligible cases (within systolic blood pressure groups), the entire control group can be used for comparison with their activation date being randomly assigned during the quarter in which the controls meeting eligibility criteria are identified. We will compare the amount of decrease in blood pressure between the intervention and control groups in both the first and second 3 month periods following activation.

A second reason for lack of effect may be that substantial numbers of patients are not willing to participate in the intervention. It is important to quantify this rate of refusal, as well as to try to estimate the effect of the intervention among compliers so that we can assess whether our intervention achieved similar benefits to prior studies among comparable populations of compliers. A naive as-treated analysis is clearly flawed as the comparability between intervention and control groups is lost when we only analyze those patients in the intervention who accepted the intervention. Thus we will carry out a complier average causal effect (CACE) analysis in which the randomization is used as an instrument to estimate the effect of the intervention among the complier population in both the intervention and control group [43].

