### Intervention

The intervention period was defined as the 14 months in which eligible patients were being identified and offered encounters with the pharmacists. Enrollment of patients occurred during months 1-14. Eligibility for the intervention was determined at the beginning of the 14-month intervention period and again at 3, 6, 9, and 12 months. At the start of each quarter, pharmacists received a list of patients with poor blood pressure control and adherence problems or inadequate medication intensification. The list was randomized within 3 blood pressure strata (> = 160, 150-159, 140-149) to allow outreach to the patients with higher blood pressure levels first. The data were then loaded into the tool used by the pharmacists (MMT) described above. Pharmacists were instructed to contact patients in the order that they appeared on their list. At the end of each quarter, if no attempts had yet been made to contact a patient (i.e., the size of the pharmacist's current patient panel was such that the pharmacist did not have time to contact that individual as well as individuals further down the list), that patient was removed from the pharmacist's list.

Prior to being contacted by the pharmacist, patients at the VA sites were notified via a letter mailed by the study team that a pharmacist would be contacting them to invite them to participate in a new clinical program, a customary VA practice for new projects and programs, and therefore required by the governing IRBs. This letter was not required by the IRB governing the KP sites because patients in KP are accustomed to being contacted by the health plan for clinical outreach.

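### The primary analysis population is stated two ways (contacted patients, eligible patients); under the contacted reading the two arms are selected differently and the comparability claim would not hold.

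*Protocol article*

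**What the plan says.** The Design Issues section of the protocol article presents its primary set as corresponding to intention to treat: "all contacted patients, regardless of whether they were successfully contacted and enrolled in the intervention, will be included in the primary analyses". It adds that patients keep the group they belonged to when first eligible, and concludes: "In this way the comparability of the patients in the intervention and control groups is maintained". The next paragraph of that section describes the principal analysis as asking whether intervention teams "had a larger sustained decline in blood pressure among patients eligible for the intervention than teams that were randomized to the control intervention".

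The Intervention section sets out how contact is allocated. Each quarterly list is "randomized within 3 blood pressure strata (> = 160, 150-159, 140-149) to allow outreach to the patients with higher blood pressure levels first", and "Pharmacists were instructed to contact patients in the order that they appeared on their list". If no attempt has been made by the end of the quarter, "that patient was removed from the pharmacist's list". Lists are drawn at the start and at months 3, 6, 9 and 12.

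Sample Size bases its calculation on an average of 275 patients per team, counted by contact or attempted contact. The primary model has terms for period, treatment, their interaction (the primary test) and site. For a secondary slope analysis, the article says that "the entire control group can be used for comparison", because activation is random within SBP groups.

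**The concern.** Eligible and contacted are the same population only if every listed patient is attempted, and the Intervention section expressly provides for patients who are not. Under the contacted reading, membership in the intervention arm depends on an event after randomization. That event is governed by SBP stratum and, for patients dropped and listed again, by still being uncontrolled later. Study outreach does not exist in control teams, and the article gives no matching rule for them.

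SBP level and persistence of high SBP both bear on the change from the pre window to the post window. Filtering one arm on them can shift the treatment-by-period interaction with no treatment effect present. The treatment main effect absorbs a difference in baseline level, but not a difference in expected change. At stake are the validity of the primary test and the statement that comparability is preserved.

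**Working it through.** **1. The two populations side by side**

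| Source in the article | Population | Defined for control teams? |
|---|---|---|
| Design Issues, intention-to-treat sentence | contacted, successfully or not | no |
| Sample Size | 275 per team, contacted or attempted | no |
| Design Issues, principal analysis | eligible patients | yes |
| Table 1, A1c and LDL | eligible patients | yes |

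**2. The plan's own figure**

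Inputs: 8 teams per arm, 275 patients per team, ICC 0.02, power 0.8, detectable difference 4.4 mmHg. Two-sided alpha 0.05 is assumed.

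- Design effect = 1 + (275 − 1) × 0.02 = 6.48.
- Effective n per arm = 8 × 275 / 6.48 = 339.5.
- Detectable difference = (1.960 + 0.842) × SD × √(2/339.5) = 0.215 × SD.

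No SD is stated, so 4.4 cannot be reproduced. It corresponds to an SD of 4.4/0.215 ≈ 20.5 mmHg, which is plausible. The implied standard error is 4.4/2.802 ≈ 1.57 mmHg. The figure serves here only as a yardstick.

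**3. Null simulation of the listing rules**

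There is no treatment effect. Everything in this paragraph except the eligibility thresholds, strata and number of pulls is assumed: mean SBP 135; one reading per quarter with SD 12; between-patient SD 12 (rows A and B), or 8 plus a slow drift of SD 9 (row C). A patient is eligible when the last reading and the mean of the last three are both at least 140. There are five pulls, with 75%, 50% or 25% of not-yet-attempted listed patients attempted at each, highest stratum first. Unattempted patients are listed again if still eligible. In rows B and C, usual care lowers SBP at each listing by 10% or 20% of the excess of the last reading over 140, identically in both arms.

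Entries are attempted minus all eligible, in mmHg. A negative change favours the intervention spuriously.

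| Setting | Fraction per pull | Share ever attempted | Baseline gap | Difference in change |
|---|---|---|---|---|
| A. Regression to the mean only | 0.75 | 0.90 | 0.71 | +0.01 |
| | 0.50 | 0.75 | 1.89 | +0.10 |
| | 0.25 | 0.49 | 4.16 | +0.07 |
| B. Usual care 10% | 0.75 | 0.90 | 0.74 | −0.31 |
| | 0.50 | 0.74 | 1.87 | −0.75 |
| | 0.25 | 0.48 | 4.02 | −1.69 |
| C. Usual care 20%, with drift | 0.75 | 0.88 | 0.71 | −0.60 |
| | 0.50 | 0.70 | 1.65 | −1.40 |
| | 0.25 | 0.43 | 3.31 | −2.89 |

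Other null runs with different assumed SDs and outreach capacities gave pooled differences within about 1 mmHg. Some of these showed attempted patients falling 0.2 to 1.0 mmHg less than all eligible patients, a bias against the intervention.

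**4. Why pooling shrinks the effect**

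At the first pull the qualifying reading lies in the pre window, so taking the highest readings first exaggerates the later fall. At later pulls the qualifying readings lie between the two windows. Patients attempted after re-listing have also stayed high, which tends to reduce their fall. The two selections work in opposite directions.

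**The case against.** The strongest reply is that the contacted sentence never says only. Its purpose is to keep refusers and unreachable patients in the analysis, and the surrounding text points to everyone eligible: the aim of measuring impact on the whole population, assignment at first eligibility, the wording of the principal analysis, and Table 1. A reader might infer that the plan definitely discards unattempted intervention patients. The article does not establish that. The contacted reading is one of two, although Sample Size supports it.

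Second, a reader might infer that primary-analysis controls are known to be unfiltered. The sentence about using the whole control group belongs to the secondary slope analysis. For the primary analysis, an unfiltered control set is an inference from the absence of any parallel rule. Handling of SBP stratum could be set out in a fuller document that is not shown.

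Third, a reader might expect a spurious benefit close to the design difference. Null simulations restricted to the first list give about 0.7 to 4.3 mmHg from regression to the mean. The plan uses five pulls, and with all five the figure is about 1 mmHg or less, of either sign.

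These replies limit the point but do not remove it. The two population statements still conflict, and the comparability sentence is correct under only one of them.

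**Conclusion.** The article states its primary population inconsistently. If the contacted set is used, intervention patients are selected by SBP-ordered outreach and by later re-listing, with no equivalent stated for controls, and the comparability claim would not hold. If every eligible patient is used in both arms, this problem disappears.

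Under the contacted reading, a higher baseline SBP among attempted patients is expected whenever some listed patients go unattempted (0.7 to 4.2 mmHg in the table). Bias in the primary contrast is less certain. With five pulls and assumed SDs it is about 1 mmHg or less from regression to the mean alone, and may disadvantage the intervention. It reaches about 3 mmHg in the intervention's favour only with a low attempted share and an assumed usual-care response that is stronger at higher SBP. Against 4.4 mmHg, these are at most about 23% (1/4.4) and 66% (2.9/4.4). The SDs, outreach capacity, attempted share and usual-care response are all assumptions, because the article gives none of them. The contradiction affects the primary test and should be resolved before analysis.

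**What to change.** Define the primary population identically in both arms: every patient on any quarterly eligibility list, analyzed in the group held at first eligibility, including intervention patients removed without an attempt. Reword the contacted sentence to match, and restate the 275 per team as listed patients.

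The change is to wording, since eligibility is determined from electronic data that do not depend on contact. The real cost is dilution. If 75% of listed patients are attempted (an assumption), an effect of 4.4 mmHg confined to them becomes 4.4 × 0.75 = 3.3 mmHg. Larger teams recover little. With 275/0.75 ≈ 367 listed per team, the design effect is 1 + 366 × 0.02 = 8.32, the effective n per arm is 8 × 367/8.32 ≈ 353, and the detectable difference is 4.4 × √(339.5/353) ≈ 4.3 mmHg.

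An attempted-contact comparison may be kept as supporting, provided each control is weighted by its cumulative attempt probability: one minus the product, over that control's listings, of (1 − attempted fraction among not-yet-attempted intervention patients in the same site, pull and SBP stratum). For two listings with fractions of 0.5, the weight is 1 − 0.5 × 0.5 = 0.75. Weights from a single cell, or fractions summed over cells, do not handle re-listing correctly. In null simulation the cumulative weights removed the bias to within 0.05 mmHg.

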## Methods

### Experimental Design Overview and Aims

This study was conducted as a cluster-randomized effectiveness study in which primary care teams, within sites, were randomized to one of two conditions: proactive case identification followed by adherence counseling and medication management delivered by a clinical pharmacist trained in behavioral counseling approaches (motivational interviewing) or usual care. This study involves the collection and analysis of both quantitative and qualitative data (the latter primarily at VA sites) during a 14 month intervention period. Qualitative data were also collected at VA sites before the intervention to assess how to make the intervention most effective and after the intervention to evaluate the implementation process, attainment, and sustainability.

Randomization occurred at the team level to evaluate the real-world effectiveness of pharmacist-team interactions rather than just the efficacy of pharmacist interactions with selected patients and to minimize cross-over contamination. At three of the study sites, existing primary care teams were randomly assigned to two intervention teams and two usual care (control) teams. At the fourth study site, the existing primary care teams were randomized to one intervention and one usual care team. At the fifth site, where a true team structure didn't exist, two artificial teams were constructed and randomized to one intervention and one usual care team, for a total of 8 intervention and 8 control teams. Each team consisted of primary care providers, their staff, and patients. All sites were recruited before randomization and then block randomized by site in order to minimize differences in baseline characteristics due to site. Randomization was done by random number generator. Thus allocation concealment was achieved at the cluster level.

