#### Sample Size

Our perspective focusing on effectiveness had a substantial impact on our sample size requirements and subsequent design decisions. Our pharmacist intervention was designed to be integrated into existing provider teams, especially with the need for substantial trust between the providers and pharmacist in order to allow the pharmacists to make medication adjustments and the ability to easily consult with providers should discussion about those adjustments be required. Thus, we needed to randomize provider teams to intervention vs. control rather than individuals.

A cluster randomized trial requires substantially larger sample sizes than a simple RCT, contingent on the amount of clustering of the dependent variable by team as measured by the intraclass correlation coefficient (ICC). We attempted to ameliorate the effect of clustering in several ways. First, the focus on difference in blood pressure as opposed to post intervention blood pressure removes much of the potential systematic patient differences in blood pressure across teams. Furthermore, we decided to randomize teams within site, essentially moving all of the between site variation in blood pressure decline to a stratification variable that can be adjusted for in the analysis. Prior work suggests that ICCs for blood pressure are well under 0.02 for physician teams, much less than for sites of care [44-48]. Furthermore, focusing on the change in blood pressure rather than a cross sectional blood pressure measurement will reduce this clustering even further.

Our sample size calculations demonstrated that with an average of 275 participants contacted (or attempted to be contacted) per team, we could detect a 4.4 mmHg difference with a power 0.8 with only 2 observed blood pressures per person in each of pre and post intervention measurement windows, under the most pessimistic assumptions of an ICC of 0.02.

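### The primary interaction model is valid but forgoes precision: with all eligible patients analysed, adjusting for baseline SBP, stratum and data pull would usually narrow the interval, by an amount the protocol does not fix

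*Protocol article*

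**What the plan says.** The protocol article, under Design Issues for analysis and sample size calculations, sets out a three-level model with BP readings "nested within patient identifier at level 2 and team at level 3". Its fixed terms are period, treatment group, their interaction and site. On the group term: "The coefficient of an indicator variable representing treatment teams will estimate the mean BP difference between treatment and controls in the baseline period". On the test: "The primary hypothesis will be tested by an interaction term between the treatment group indicator and the time period indicator variables". On covariates: "Site will be included as a fixed variable". No term for SBP stratum or for the quarter of first eligibility is named.

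The Sample Size section gives the reason for analysing change: "the focus on difference in blood pressure as opposed to post intervention blood pressure removes much of the potential systematic patient differences". It compares change with post-intervention BP alone. Post-intervention BP adjusted for baseline is not discussed. The design has five sites "for a total of 8 intervention and 8 control teams", and the calculation states that "with an average of 275 participants contacted (or attempted to be contacted) per team" and an ICC of 0.02, "we could detect a 4.4 mmHg difference with a power 0.8".

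Three other statements bear on this. Patients qualify on SBP thresholds of 140 or 150 (Inclusion criteria). Eligibility is assessed at the start and at months 3, 6, 9 and 12, and pharmacists work from the highest SBP stratum down (Intervention). The Design Issues section describes the analysed patients both as those contacted and as those eligible.

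**The concern.** A free group term plus an interaction makes the estimate, in balanced data, the difference in mean change. That subtracts the whole baseline value. When pre and post values are only moderately correlated, this over-corrects: a team that starts high by chance tends to fall more through regression to the mean, and that fall enters the estimate. Selecting patients on high SBP weakens the correlation. With 16 teams, some chance imbalance at baseline is likely.

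Change should also depend on the data pull. Patients first eligible at month 0 qualify on readings that overlap the pre-intervention window, so their SBP should regress downward. Patients first eligible at month 12 qualify on readings taken after that window. Stratum and pull are known for every eligible patient. What is at stake is the width of the primary confidence interval.

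**Working it through.** **Inputs.** From the Sample Size and design sections: 8 teams per arm, 275 patients per team, ICC 0.02, detectable difference 4.4 mmHg, power 0.80. Assumed, because not stated: two-sided alpha 0.05; total variance 200, split into tau² = 4 (team) and s² = 196 (patient), so that 4/200 = 0.02; patient pre/post correlation r = 0.25 to 0.40; team pre/post correlation rc = 0.3 to 1.

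**The plan's own figure.** The design effect is 1 + 274 × 0.02 = 6.48. Effective n per arm is 2200/6.48 = 339.5. A detectable difference of 4.4 needs SE = 4.4/2.80 = 1.57, hence SD = 1.57 × √(339.5/2) ≈ 20.5 mmHg. No SD is stated, so 4.4 can be back-solved but not verified.

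**Does 4.4 presuppose team-level variation in change?** If team effects were identical in both periods they would cancel from the interaction. Then SD of change = 1.57 × √(2200/2) = 1.57 × 33.2 ≈ 52 mmHg, which is implausible. The plan's figure therefore implies rc below 1, although the model as described names no team-by-period effect.

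**Efficiency.** Treatment varies only by team, so the comparison rests on team means. Let a = tau² + s²/275 = 4 + 0.713 = 4.713 and c = rc × tau² + r × s²/275.
- Variance per team, free baseline: 2(a − c).
- Variance per team, common baseline: a − c²/a.
- SE ratio: √[(1 + c/a)/2].

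| rc | c (r = 0.25 to 0.40) | SE ratio |
|---|---|---|
| 0.3 | 1.378 to 1.485 | 0.80 to 0.81 |
| 0.5 | 2.178 to 2.285 | 0.86 |
| 0.8 | 3.378 to 3.485 | 0.93 |
| 1.0 | 4.178 to 4.285 | 0.97 to 0.98 |

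A parameterisation with two readings per window and a patient variance share of 0.2 to 0.6 agrees: 0.86-0.88 at rc 0.5, 0.93-0.94 at 0.75, 0.98-0.99 at 1.

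**A caution on ANCOVA.** These ratios need the baseline slope to be right at team level (c/a). ANCOVA using only each patient's own baseline applies a slope near r, with variance a(1 + r²) − 2rc′, where c′ is c above. At rc 0.8 and r 0.25 this is 4.713 × 1.0625 − 0.5 × 3.378 = 3.318, against 2(4.713 − 3.378) = 2.670 for change: an SE ratio of √(3.318/2.670) = 1.11, a loss. At rc 0.3 and r 0.25 it is 5.007 − 0.689 = 4.318 against 6.670, a ratio of 0.80.

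**Patient-level simulations with no treatment effect.** On all eligible patients, baseline adjustment cut the SD from 14.1 (change) to 12.2, from 12.1 to 10.9, and from 19.1 to 15.4 mmHg in three assumed settings. A separate simulation gave about 11.9 to 10.2-10.7, and stratum-by-pull terms on change alone gave 10.6-10.9. Adjusted estimates were unbiased. On top of baseline adjustment, stratum-by-pull terms added almost nothing (12.2 v 12.2; 15.4 v 15.3).

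**Contacted patients only.** With assumed contact rates of 25-50%, 60-80% and 100% from lowest to highest stratum, and all controls kept, the arms differed at baseline by 0.9 to 2.7 mmHg. The planned model was biased by −0.3 to −1.0 and baseline adjustment alone by +0.2 to +0.8. With stratum-by-pull terms both were within about 0.1 of zero. In the separate simulation, baseline adjustment gave +0.4 to +0.9 where the planned model had almost none.

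**The case against.** The choice is deliberate. The principal question is whether intervention teams show a larger sustained decline, and group-by-period in a multilevel model is a standard test of that. The analysis plan is not shown and may add covariates. The model also weights patients by their number of readings, so calling it a pure change-score test is exact only for balanced data. All of this stands: the planned model is not an error.

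The strongest objection is that a common baseline assumes equal expected baselines. Patients are identified after teams are randomized, four of the five pulls come after the programme starts, and contact is ordered by SBP. On the contacted set the constraint replaces one bias with another. That limits where the fix applies. It does not remove the gain when all eligible patients are analysed.

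The protocol also expects clustering to be lower for change than for a single measurement. That points to a high team correlation and a gain at the small end of the range.

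A reader might infer that the adjustment comes free, or that the detectable difference would drop to about 3.5-4.0 mmHg. Neither is supported. The first ignores the assumption above. The second multiplies 4.4 by ratios from inputs that do not produce 4.4: with tau² = 4 and s² = 196, the change-score detectable difference is 2.80 × √[(a − c)/2], or 3.6 mmHg at rc 0.3 (r 0.25) and 2.2 at rc 0.8 (r 0.40).

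**Conclusion.** The point holds as an efficiency recommendation. The planned test is valid, but it uses the baseline less efficiently than it could, and the stated rationale does not consider baseline-adjusted post-window SBP. The SE ratio is about 0.80-0.86 at team correlations of 0.3 to 0.5, 0.93 at 0.8 and 0.97-0.98 at 1. The document does not say where in that range the trial lies. Its 4.4 mmHg figure implies a correlation below 1.

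The conclusion rests on the assumed variances and correlations, on analysing all eligible patients in both arms, and on pre-window SBP having the same expectation in both arms. Stratum and pull terms explain change if used alone. Once baseline is adjusted for, they add little precision and serve mainly to guard against differences in case mix.

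**What to change.** In the analysis of all eligible patients in both arms:

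1. Adjust post-window SBP for pre-window SBP. Either fit the multilevel model with a common baseline mean (drop the treatment main effect and keep the treatment term in the post period) and a team-by-period random effect, or use ANCOVA with both the patient's pre-window SBP and its team mean.
2. Add SBP-stratum-by-period and first-eligible-pull-by-period fixed terms. As main effects alone they would leave the interaction's standard error essentially unchanged.
3. Keep the planned free-baseline interaction model as a sensitivity analysis.
4. Do not apply the baseline constraint to the contacted-only set.

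No new data are needed, because the readings, strata and pulls are already held. The costs are reliance on equal expected baselines despite four pulls after the programme starts, and a few degrees of freedom. With 16 teams and 5 sites, about 16 − 5 − 1 = 10 remain at team level, and a team-mean covariate uses one more.
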